### Data Handling and statistical analysis

Name and address details were maintained in Microsoft Access. Check boxes recorded the progress of a participant through the study and thus allowed personalised letters to be sent to groups of participants as required throughout the study. All other data were entered into a single Microsoft Excel spreadsheet with participants identified only by their unique Subject Number. All entries were double-checked by another member of the research team.

Before commencement of statistical analysis the data will be cleaned and checked for coding errors. Descriptive statistics will be used for the baseline population characteristics: mean (SD), median, mode and range summary statistics, independent t-tests and paired t-tests for numerical normally distributed data, and Mann Whitney U and Wilcoxon Paired Rank Test (for paranormal distribution) and Chi-Squared tests (for categorical data). Spearman (checked with Pearson) correlations and ANOVA will be calculated to test for associations between variables.

The primary analysis will be a comparison of the change of the primary outcome (vitamin D status) between the intervention and the control group following the 'intention to treat' principle at three months and six months. In order to assess whether protocol deviations have caused bias, the results of the intention-to-treat analyses will be compared to 'per protocol' analyses. Furthermore secondary analyses will be performed to explore intervention effects on the insulin resistance, HDL/triglycerides and bone markers. Analysis of covariance will be used to analyse the effects of treatment on changes in variables while controlling for the effects of possible confounding factors for example different baseline conditions (e.g. BMI). Statistical analyses will be performed by using SPSS software (version 15).

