**Discussion:**

This randomised, controlled trial will be the first to investigate the effect of vitamin D supplementation on insulin resistance in non-diabetic subjects. It will subsequently contribute to the growing body of evidence about the role of vitamin D in metabolic syndrome.Registered clinical.

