### Aims

• To establish the vitamin D status of South Asian women living in Auckland, NZ.

• To investigate the effectiveness of vitamin D supplementation in improving insulin sensitivity in women with hypovitaminosis D who have demonstrated insulin resistance, and/or lipid profiles in those with dyslipidaemia.

• To investigate the effect of vitamin D supplementation on bone marker ratios in women who have hypovitaminosis D.

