### Participants

It was calculated that 42 subjects would be required for each arm of the trial to demonstrate a significant difference at 80% power and 5% significance. Power calculations were based on the results of a lifestyle intervention which achieved a reduction in HOMA-IR of 0.98 [28], and derived from Margetts and Nelson [29].

Women were invited to participate in the study through advertisements in suburban and Auckland newspapers, and Indian media such as television, radio and newspapers. Posters and leaflets were distributed in a number of venues around Auckland such as General Medical Practices with high numbers of South Asian patients, clubs, and temples. A number of South Asian social and community groups were given presentations about the study by the researchers.

A short television documentary on a channel popular with Indian viewers elicited the greatest response of all the methods used. However, the most effective form of promotion was word-of-mouth. A relatively small group of supportive women from the South Asian community promoted the study and were instrumental in the successful recruitment of 250 women.

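### The declared primary outcome (vitamin D status) mainly measures exposure, while the trial's question and its only power calculation concern HOMA-IR

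*Protocol article*

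**What the plan says.** The section on data handling and statistical analysis fixes the primary outcome outright: "The primary analysis will be a comparison of the change of the primary outcome (vitamin D status) between the intervention and the control group". The comparison is by intention to treat and is made at both follow-up visits, 3 and 6 months. It continues: "Furthermore secondary analyses will be performed to explore intervention effects on the insulin resistance, HDL/triglycerides and bone markers".

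The Participants section sizes the trial on a different variable. It says that "42 subjects would be required for each arm of the trial to demonstrate a significant difference at 80% power and 5% significance". The variable behind that figure is given next, in the source of the effect size: "Power calculations were based on the results of a lifestyle intervention which achieved a reduction in HOMA-IR of 0.98". It gives no SD, and no effect size or SD for 25(OH)D appears anywhere in the article.

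The second aim is "To investigate the effectiveness of vitamin D supplementation in improving insulin sensitivity in women with hypovitaminosis D who have demonstrated insulin resistance", extended to lipid profiles in women with dyslipidaemia. The third aim concerns bone marker ratios. The Abstract describes the trial as "the first to investigate the effect of vitamin D supplementation on insulin resistance in non-diabetic subjects".

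**The concern.** The statistical section and the rest of the article describe two different trials. One tests whether women given vitamin D end up with more of it in their blood than women given placebo. The other tests whether vitamin D improves insulin resistance. The second is the one that was motivated, recruited for and sized.

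Two things are at stake. First, a primary result that is close to certain says little: the trial could be reported as having met its primary outcome while HOMA-IR did not move. Second, a genuine HOMA-IR effect, the one the sample was sized to find, would be reported as a secondary result from an analysis the plan itself describes as exploring effects.

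**Working it through.** **1. Which outcome does each part of the article support?**

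| Place in the article | Outcome it concerns |
|---|---|
| Hypotheses, first | Prevalence of low vitamin D in the population (descriptive) |
| Hypotheses, second | Markers of metabolic syndrome |
| Hypotheses, third | Bone marker ratios |
| Aims, first | Vitamin D status of the population (descriptive) |
| Aims, second | Insulin sensitivity and/or lipid profiles |
| Aims, third | Bone marker ratios |
| Abstract, Methods | HOMA-IR, lipids, parathyroid hormone, calcium, bone markers; 25(OH)D is not among the monitored changes listed |
| Abstract, Discussion | Insulin resistance |
| Participants (sample size) | HOMA-IR, reduction of 0.98 |
| Discussion | Insulin resistance, metabolic syndrome, aetiology of type 2 diabetes |
| Statistical analysis, primary | Vitamin D status |

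Only the last row makes 25(OH)D an outcome of the randomised comparison. The first hypothesis and first aim describe the screened population and compare no arms.

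**2. What does 25(OH)D measure here?** Entry required 25(OH)D below 50 nmol/L. The active capsules were assayed at a mean of 4226 IU per dose, and no vitamin D was detected in the placebo (Vitamin D intervention). A difference in serum 25(OH)D is what the capsules directly supply. Its size depends on adherence, absorption and vitamin D from elsewhere, not on any metabolic response.

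**3. The stated 42 per arm.** With no SD given, 42 cannot be reproduced forward; it can only be solved backwards. Inputs: n = 42 per arm, 80% power and 5% significance (Participants), and a difference of 0.98. Assumptions: the test is two-sided and the 0.98 is a between-arm difference, neither of which is stated.

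- Two-sample t-test, noncentrality d × √(n/2), with √(42/2) = 4.583 and 82 degrees of freedom. Power of 80% needs d = 0.619, so the implied SD is 0.98 / 0.619 = 1.58.
- Normal approximation as a cross-check: d = (1.960 + 0.842) × √(2/42) = 0.611, so SD = 0.98 / 0.611 = 1.60.

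Both give an SD of about 1.6. The remaining figures all use the t-test.

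**4. Power for a HOMA-IR difference of 0.98 at 42 per arm, by assumed SD**

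| SD (assumed) | d = 0.98 / SD | Power |
|---|---|---|
| 1.25 | 0.784 | 94% |
| 1.58 | 0.620 | 80% |
| 2.0 | 0.490 | 60% |

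**5. Power for 25(OH)D at 42 per arm, by assumed standardised difference**

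| Difference in SDs (assumed) | Power | n per arm for 80% power |
|---|---|---|
| 1.0 | 99.5% | 17 |
| 1.2 (e.g. 30 nmol/L, SD 25) | 99.97% | 12 |
| 1.6 (e.g. 40 nmol/L, SD 25) | >99.99% | 8 |

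The nmol/L values are illustrations and do not come from the article. If the shift is 1 SD or more, the trial is at least 42 / 17 ≈ 2.5 times as large as its declared primary comparison needs.

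**The case against.** The strongest defence is that HOMA-IR is not neglected. It is scheduled at baseline, 3 and 6 months, it will be compared between arms, and analysis of covariance is available. In a condensed article, describing secondary analyses as exploring effects may be loose wording, and a testing hierarchy could sit in an analysis plan that is not shown. This stands to a degree. A reader might infer that the trial leaves its own question unexamined, or that a positive HOMA-IR result could never be treated as confirmatory; the document supports neither. But the article states which outcome is primary, and that statement conflicts with its own sample-size paragraph whatever another document says.

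A second defence is that 25(OH)D shows more than absorption. That is right. It also captures adherence and outside vitamin D: three women were lost because a practitioner prescribed vitamin D, and the capsules are to be retested for degradation. Separation between arms is worth knowing, but as evidence of exposure rather than efficacy.

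Third, the aims do not point to HOMA-IR alone. Lipids and bone markers are named too, women could enter through raised insulin, raised glucose or the triglyceride/HDL-C ratio without HOMA-IR above 1.93, and the primary analysis is set at both 3 and 6 months. HOMA-IR is still the best-supported candidate because it is the only variable with a power calculation. The choice of 6 months is a recommendation, not something the text dictates.

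A reader might also infer that the trial is underpowered for HOMA-IR or that 42 is wrong. The article gives no SD, so neither can be shown. Nor can anything be said about which primary outcome the registry holds: only the registration number is given.

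**Conclusion.** The point holds as an internal contradiction in the protocol article. The stated primary outcome matches no hypothesis or aim of the randomised comparison and has no link to the sample size, and a positive result on it would not show that vitamin D improves insulin resistance. The near-certainty of that result (power above 99%) rests on an assumed 25(OH)D difference of at least 1 SD. The corresponding power for HOMA-IR rests on an unstated SD of about 1.6, and on reading the 0.98 as a between-arm difference with a two-sided test. The contradiction itself depends on none of these assumptions. It should be corrected before unblinding, because it determines what the trial's main result can claim.

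**What to change.** By dated amendment before unblinding, reconcile the statistical section with the Participants section:

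- Name the between-arm difference in change in HOMA-IR at one stated time point as the single primary outcome. Six months, the end of the intervention, is the natural choice.
- Report serum 25(OH)D at 3 and 6 months as a measure of exposure.
- Keep lipids and bone markers as secondary outcomes.
- State the SD behind 42 per arm, and whether the 0.98 is a between-arm difference or a within-group change.
- Check the amended wording against the registry entry and align the two if they differ.

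The cost is a few sentences. The sample size does not change, because 42 per arm is already tied to HOMA-IR, and HOMA-IR is already scheduled at every visit, so no new data or participants are needed. The article puts the analysis in the future tense and tells participants their allocation only on completion, so the change looked feasible when it was written. If unblinding has since taken place, the report should state when the primary outcome was settled.

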**Questionnaires:**	
Dietary assessment	4-day food diary. Completed by subjects. Analysed using Foodworks 2007 (Xyris Software). Additional recipes and food lists provided by Indian dietitian
Medical and family history	Questionnaire administered following blood tests
Demographics	

One hundred and six women were recruited for phase 2, but a number were lost to the study due to becoming pregnant (n = 3), moving overseas (n = 6) perceived side-effects (n = 2), medical practitioner prescribing vitamin D (n = 3), or withdrew from study (n = 8).

The intervention consisted of a 25(OH)D_3 _supplement, 4000 international units (IU) per day, or placebo, in the form of 4 oral capsules, for 6 months. The consumption of 4000 IU 25(OH)D_3 _has been shown to be a safe and effective dose [32,33]. The active supplement was tested for 25(OH)D_3 _content by the Massey University Nutrition laboratory. The average content per dose was 4226 IU, no vitamin D was detected in the placebo. The vitamin D content will be tested again at the completion of the study to determine any degradation during storage over the period of the study.

Subjects were matched into pairs by age and BMI. Randomisation of the active/placebo capsules and allocation to pairs was performed by Blackmores using nQuery Advisor^®^, version 6.0, (Statistical Solutions, Cork, Ireland). Randomisation and allocation were fully concealed from the researchers.

Once recruited into phase two, participants were recalled for a baseline blood test prior to being given their supply of supplements. After 3 months another blood sample was taken to check for hypercalcaemia. Once the intervention was completed (6 months) participants provided one more blood sample and were weighed again. See Table 2 for outcome measures and testing methods for the intervention phase of the study.

**Table 2 T2:** Outcome measures and testing method for phase two (measured at baseline, 3 months and 6 months)

**Test**	**Method**
Blood tests As listed in table 1, plus:	
Collagen C-telopeptide (CTX) Osteocalcin (OC)	Roche Elecsys beta cross-laps Roche Elecsys 2010 Canterbury District Health Board Laboratory
Weight at baseline and 6 months	Tanita electronic scales

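### The primary comparison of change carries no stated covariate; naming ANCOVA with the outcome's own baseline value, age and BMI as the primary model would gain precision at no cost

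*Protocol article*

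**What the plan says.** The relevant text is in the protocol article, Data Handling and statistical analysis. The primary analysis is a between-arm comparison of change in vitamin D status, by intention to treat, at three and six months. That sentence names no model and no covariate. Insulin resistance, the lipid ratio and bone markers are secondary.

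A later sentence brings in analysis of covariance with change as the response, "controlling for the effects of possible confounding factors for example different baseline conditions (e.g. BMI". BMI is the only covariate named, and it is given as an example. The section does not say whether this ANCOVA is the primary analysis or supports it.

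Two statements under Vitamin D intervention bear on the choice of covariates. The first is "Subjects were matched into pairs by age and BMI", so age and BMI are design factors. The second is that "participants were recalled for a baseline blood test prior to being given their supply of supplements", so a pre-treatment value of every blood outcome exists.

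**The concern.** In a randomised trial, baseline differences between arms arise by chance. The main reason to adjust is therefore precision, and covariates are best fixed in advance for how well they predict the outcome. The baseline value of the outcome is usually the strongest candidate. The article presents adjustment as control of confounding, gives as its one example a variable already balanced by the matching, and mentions neither the outcome's own baseline value nor age, the other matching factor.

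Two things are left open: whether the baseline value is in the model, and which of the two analyses gives the primary result. If the primary comparison is carried out as written, on change alone, a trial of 84 women gives up precision that it could have from data in hand.

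**Working it through.** **The plan's own figure.** Under Participants, "42 subjects would be required for each arm of the trial" at "80% power and 5% significance", "based on the results of a lifestyle intervention which achieved a reduction in HOMA-IR of 0.98". No SD is stated, so 42 cannot be reproduced. It can only be back-solved, using the two-sample normal approximation and taking 0.98 as the between-arm difference:

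SD = 0.98 × √(n/2) / (z_α + z_0.80)

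- Two-sided, n = 42: 0.98 × 4.583 / (1.960 + 0.842) = 1.603. With n = 41 the result is 1.584, so rounding up to 42 is compatible with about 1.58 to 1.60.
- One-sided, by the same formula: about 1.78 to 1.81.

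The article does not say whether such an SD would belong to a change or to a single measurement.

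**Change score against baseline-adjusted ANCOVA.** Let the outcome have variance σ² at both baseline and follow-up, with correlation ρ between them. Equal variances are an assumption, and ρ is not in the article.

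- Variance of the change: 2σ²(1−ρ)
- Residual variance after adjusting for baseline: σ²(1−ρ²)
- Ratio, ANCOVA to change: (1−ρ²) / [2(1−ρ)] = (1+ρ)/2
- Reduction: (1−ρ)/2

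| Assumed ρ | Ratio | Variance reduction | Women per arm for the precision of 42 on change (42 × ratio, rounded up) |
|---|---|---|---|
| 0.3 | 0.65 | 35% | 28 |
| 0.5 | 0.75 | 25% | 32 |
| 0.7 | 0.85 | 15% | 36 |
| 0.9 | 0.95 | 5% | 40 |

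**Without equal variances.** With SDs σ₀ at baseline and σ₁ at follow-up, the variance of the change minus the ANCOVA residual variance is

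σ₀² + σ₁² − 2ρσ₀σ₁ − σ₁²(1−ρ²) = (σ₀ − ρσ₁)².

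This is never negative. The direction of the result therefore does not depend on equal variances, but its size does: the gain vanishes if σ₀ happens to equal ρσ₁.

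**Why no power figure follows.** Take 1.603 and 42 per arm for HOMA-IR under the two possible readings of that SD:

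| ρ | SD is of change: change / ANCOVA power | SD is of one measurement: change / ANCOVA power |
|---|---|---|
| 0.3 | 80% / 93.5% | 65.8% / 83.6% |
| 0.5 | 80% / 89.9% | 80.0% / 89.9% |
| 0.7 | 80% / 86.0% | 95.1% / 97.5% |

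ANCOVA is ahead in every row, but the level depends on a back-solved SD, on its interpretation and on an assumed ρ. The table also concerns HOMA-IR, which the analysis section makes secondary. For vitamin D status, the article gives nothing to compute from.

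**Validity.** In a simulation with 42 per arm and no treatment effect (10,000 runs), the type I error at ρ = 0.5 and 0.7 was 5.0% and 5.0% for the change score, and 4.8% and 4.8% for prespecified ANCOVA. Both are sound; they differ in precision.

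**The case against.** The strongest reply is that the article does plan ANCOVA and gives its covariates only as examples. The baseline value of the outcome is itself a baseline condition, so it may well be included. If it is, ANCOVA on change and ANCOVA on the follow-up value give the same treatment estimate, and nothing is lost. A comparison of change is also unbiased, and a condensed article may leave the exact covariates to an analysis plan that is not shown. All of this stands, and it is why the point is an improvement and not an error. It does not remove the point: the article itself fixes change as the primary comparison without a covariate, and leaves unclear whether the ANCOVA has primary status.

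Three stronger readings are tempting, and the article does not support them.

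- *Covariates will be chosen by baseline significance tests.* A reader might infer this from the word *different*, but no sentence makes a baseline test a step in model choice. In the same simulation, adjusting only after a significant baseline difference gave a type I error of 4.3% and 4.6%, slightly conservative. Inflation, to 7.1% and 6.6%, appeared only when the smaller of the adjusted and unadjusted p-values was reported, which the article does not propose.
- *The treatment test will switch between parametric and rank methods.* The list that includes "independent t-tests and paired t-tests for numerical normally distributed data" is introduced as description of baseline characteristics, not as the rule for the treatment comparison.
- *Selecting women on extreme screening values distorts the change.* A fresh baseline sample was taken after screening, which weakens the argument. Any remaining regression to the mean acts on both arms and does not bias their difference. HOMA-IR above 1.93 was also only one of several alternative entry criteria.

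**Conclusion.** The point holds as a free improvement. The primary comparison of change, as stated, is valid, but it is less precise than ANCOVA that includes the baseline value of the outcome. With equal variances, the avoidable variance is (1−ρ)/2 of the change-score variance: 35% at ρ = 0.3, falling to 5% at ρ = 0.9. These correlations are assumptions, and the loss arises only if the baseline value is in fact left out. A reader might go further and infer that the trial is underpowered or that its treatment estimate is biased. Neither can be shown, because the article gives no SD and no correlation, and randomisation protects the comparison of change. The ambiguity over which analysis is primary is real whichever way the covariates are settled.

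**What to change.** State one primary model. Suggested wording: *The primary analysis of vitamin D status at 3 and at 6 months is an analysis of covariance with treatment, the baseline value of vitamin D status, age and BMI as terms. The secondary outcomes are analysed in the same way, each with its own baseline value. The covariates are fixed before unblinding and are not chosen from observed differences between the arms. The unadjusted comparison of change is supportive.*

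The response may be the follow-up value or the change, since the treatment estimate is the same once the baseline value is in the model.

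Two additions are optional: a log scale for outcomes expected to be skewed, such as HOMA-IR, and the season of the baseline sample as a further covariate. If used, they should be fixed at the same time.

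The cost is a change of wording. The baseline blood values, age and BMI are already collected, and the article speaks of the analysis as still to come.

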## Background

Hypovitaminosis D is becoming recognised as a worldwide problem, and exists even in countries such as New Zealand and Australia which enjoy plentiful sunshine and latitudes sufficiently moderate to allow some endogenous synthesis throughout the year [1-5]. Once thought to impact only on bone health, there is now evidence to implicate vitamin D deficiency in a plethora of adverse health conditions such as cancer and auto-immune diseases. There is mounting interest in the role of vitamin D in the constellation of metabolic abnormalities grouped under the term "metabolic syndrome", including hypertension, dyslipidaemia, abdominal obesity, glucose intolerance and type 2 diabetes.

Low serum vitamin D has been shown to correlate with impaired glucose tolerance [1,6-8], whilst administration of supplemental vitamin D to subjects with elevated blood glucose levels has resulted in an improvement in insulin secretion [9,10]. Similar improvements have been observed in vitamin D-deficient subjects following supplementation [6,11].

The role, if any, that vitamin D deficiency plays in insulin resistance has had little investigation. Whilst a correlation between hypovitaminosis D and insulin resistance has been identified in pregnant women [12] and obese adolescents [13] randomised, controlled trials with vitamin D supplementation are sparse, especially in non-diabetic, insulin resistant, vitamin D deficient subjects. Borissova et al [10] measured a 29% (but not significant) decrease in HOMA-IR following supplementation of 1332IU 25(OH)D_3_/day for one month in a group of 10 diabetic women, 70% of whom were vitamin D deficient (<50 nmol/L). Pittas et.al. [14] saw a significantly lower increase in HOMA-IR in vitamin D/calcium supplemented subjects with impaired fasting glucose, compared to those receiving calcium only, but subjects were not vitamin D deficient. Meanwhile, Taylor [15] reported an increase in insulin resistance in 3 diabetic patients following a single intramuscular dose of 300,000 IU of 25(OH)D_2_.

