### Vitamin D intervention

Initial screening (phase 1 of the study) took place over a period of 9 months, commencing February 2007. See Table 1 for outcome measures and testing methods for phase 1. From the 250 women screened in phase 1, 116 qualified for phase 2, with the inclusion criteria described above. Women with FPG >7.2 mmol/L were offered a second blood test, and then withdrawn from the study and referred to their medical practitioner if the second blood test yielded similar results.

**Table 1 T1:** Outcome measures and testing methods used for phase one.

**Measure**	**Method**
**Blood analysis**	All analysed by LabPlus, Auckland City Hospital, Auckland
Fasting plasma insulin	Micro-particle enzyme immunoassay technology (MEIA), Abbott Diagnostics
Fasting plasma glucose	An enzymatic colourimetric assay; Roche Glucose reagent kit (Cat. No. 1876899)
Total cholesterol	Enzymatic colourimetric method (Roeschlau and Allain). Roche Cholesterol reagent kit (Cat. No. 1491458)
Triglycerides	Enzymatic conversion. Roche Triglycerides reagent kit (Cat. No. 1727711)
HDL-C	Homogenous enzymatic colourimetric assay. Roche HDL-Cholesterol Plus reagent kit (Cat. No. 04713214)
LDL-C	Calculated
Serum calcium	Colourimetric assay. Roche Calcium reagent kit (Cat. No. 1730240)
Serum albumin	Colourimetric assay. Roche Albumin Plus reagent kit (Cat. No. 1970909)
Serum high sensitivity CRP	Particle enhanced immunoturbidimetric assay. Roche CRPLX reagent kit (Cat. No. 03002039)
Serum parathyroid hormone	"ECLIA" electrochemiluminescence immunoassay. PTH Reagent Pack (Cat. No. 11972103122)
Serum 25 OH vitamin D	Radioimmunoassay, DiaSorin RIA kit (Cat. No. 68100E)

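### Calendar time of sampling, a predictable source of variance in the vitamin D primary outcome, is not named for pairing or adjustment; this costs precision but not validity

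*Protocol article*

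**What the plan says.** Under Data Handling and statistical analysis, the primary analysis is a "comparison of the change of the primary outcome (vitamin D status) between the intervention and the control group", by intention to treat, at three and six months. Table 1 shows that vitamin D status is measured as serum 25(OH)D. The same section plans analysis of covariance to control for "possible confounding factors for example different baseline conditions (e.g. BMI". BMI is the only covariate named, and it is given as an example.

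On timing, the Vitamin D intervention section says: "Initial screening (phase 1 of the study) took place over a period of 9 months, commencing February 2007". The trial baseline is a separate, later sample: "Once recruited into phase two, participants were recalled for a baseline blood test prior to being given their supply of supplements". The article does not say over what period those baseline samples were taken. Treatment is taken "in the form of 4 oral capsules, for 6 months", with a further sample at 3 months.

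On design: "Subjects were matched into pairs by age and BMI". Neither date nor season of entry is mentioned.

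The Background ties vitamin D status to sunshine, with "latitudes sufficiently moderate to allow some endogenous synthesis throughout the year", and lists low sun exposure among the possible reasons for deficiency.

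**The concern.** A 6-month change compares opposite points of the annual cycle. A woman whose baseline falls in late summer is followed into late winter, so her seasonal drift is downward. A woman who starts in late winter drifts upward. If baseline dates are spread out, this drift differs between women for reasons unrelated to treatment and adds to the variance of the primary outcome. Members of a pair matched on age and BMI can start in different seasons, so the pairing does not remove it.

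The plan already applies this reasoning elsewhere. Under Blood sampling and processing, draws are held to a fixed hour in the morning because bone markers vary over the day. Calendar time gets no similar treatment for the primary outcome. At stake is the width of the confidence interval for the vitamin D effect, and secondarily for PTH and the bone markers, which may follow vitamin D over the year.

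**Working it through.** **The plan's own figure.** The Participants section states that "42 subjects would be required for each arm of the trial to demonstrate a significant difference at 80% power and 5% significance". That calculation concerns a HOMA-IR reduction of 0.98 and gives no SD. Solved backwards, two-sided, it implies an SD of about 1.60. It does not bear on serum vitamin D, for which the article gives no effect size, SD or seasonal amplitude.

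**Inputs**
- From the article: 42 per arm, samples at 0, 3 and 6 months, 9 months of screening from February.
- Assumed: seasonal amplitude A (mean to peak) of 10 nmol/L, range 5-15, the same in both arms; non-seasonal SD of change s of 15-20 nmol/L; baseline draws uniform over 9 months; seasonal peak at the start of that window.

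**Seasonal variance of the 6-month change.** Let t be the baseline date as an angle, uniform from 0 to 3π/2. The seasonal part of the change is A[cos(t+π) − cos t] = −2A cos t.
- E[cos t] = sin(3π/2)/(3π/2) = −0.212, and E[cos² t] = 0.5.
- Var(cos t) = 0.5 − 0.045 = 0.455, so the seasonal variance is 4 × 0.455 × A² = 1.82A².
- At A = 10 this is 182, an SD of 13.5 nmol/L.

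Moving the peak to mid-February gives 2.12A². At 3 months, with that same peak, it is 1.17A².

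**Share of variance at 6 months** = 1.82A²/(1.82A² + s²)

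| A | s | share |
|---|---|---|
| 10 | 15 | 182/407 = 45% |
| 10 | 20 | 182/582 = 31% |
| 5 | 20 | 45.5/445.5 = 10% |
| 15 | 15 | 409.5/634.5 = 65% |

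**Standard error of the arm difference** = √(variance × 2/42), at A = 10
- Season left in: √(407/21) = 4.4 and √(582/21) = 5.3 nmol/L.
- Season removed: √(225/21) = 3.3 and √(400/21) = 4.4 nmol/L.
- The seasonal component alone is √(182/21) = 2.9 nmol/L. It is already inside the 4.4-5.3 and is not an additional harm.

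**Shorter trial entry.** With baseline draws over 3 months, the coefficient falls to between 0.03 and 0.73, depending on where the window lies in the year. At A = 10 the share is then 3/403, about 1%, to 73/298, about 24%.

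**Baseline 25(OH)D as a covariate.** In this model the seasonal change is −2 times the seasonal part of the baseline value, so adjusting for baseline removes part of it. With an assumed non-seasonal baseline SD of 8-12 nmol/L, the fraction removed is 45.5/(45.5+64) = 42% to 45.5/(45.5+144) = 24%. The remaining share is about 21-38%, in place of 31-45%.

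**Validity and power.** In 20,000 simulated trials with season ignored (A = 12.5, s = 15), the type I error was 5.1% and the mean bias about zero. With s = 15 and 42 per arm:
- For an assumed true difference of 20 nmol/L, power stays above 99% even if the variance doubles.
- For 10 nmol/L, power falls from 86% to 75%, 70% or 58% as the variance rises by a third, by a half, or doubles.

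**The case against.** The strongest reply is that nothing here is stated wrongly. The covariate list is illustrative, the exact set is normally fixed in an analysis plan, and that plan is not shown. A reader might infer that the protocol rules out adjustment for season; the wording does not support that. Season is unnamed, not excluded.

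A reader might also infer that trial entry itself was spread over nine months. The article gives nine months for phase 1 screening only, and the result depends heavily on the unstated spread of baseline dates. Nor do the documents support any particular share of variance, such as a third to a half, because they give neither an amplitude nor an SD. Some of their content points to a smaller swing: sun avoidance in this population, entry restricted to values below 50 nmol/L, and some synthesis all year round.

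Finally, part of the gain may already be available if the planned adjustment for baseline conditions includes baseline 25(OH)D. Randomisation protects the test in any case, and power is ample if the supplement raises serum vitamin D by 20 nmol/L or more with s = 15.

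All of this stands, and it limits the size and tone of the point. What remains is that an open covariate list is a weak place to leave an obvious prognostic factor for the declared primary outcome. Date adjustment is convincing only if it is named before unblinding, and the better model is nearly free.

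**Conclusion.** This is a precision improvement of low to moderate weight. The primary outcome is a change in serum vitamin D, and calendar time of sampling appears neither in the pairing nor among the named covariates. The loss is in the standard error. A reader might infer that the treatment effect is seasonally biased; randomised allocation rules that out in expectation, and chance imbalance is already counted in the standard error.

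The size is conditional. It is about 10-65% of the 6-month variance for amplitudes of 5-15 nmol/L, SDs of 15-20 nmol/L and a 9-month spread of baseline draws. It is about 1-24% at an amplitude of 10 nmol/L if entry took about 3 months, and less once baseline 25(OH)D is in the model. The amplitude, the SD and the entry spread are all assumptions.

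**What to change.** Before unblinding, specify the analysis of covariance for 25(OH)D at 3 and at 6 months with these terms:
- treatment arm;
- baseline 25(OH)D;
- the matching variables, age and BMI;
- the calendar date of the baseline draw, as one sine and one cosine term with a 12-month period.

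Because follow-up samples fall at fixed intervals, A[cos(t+φ) − cos t] is a linear combination of sin t and cos t. The same two terms therefore serve both time points, and no peak month has to be assumed. Use the same date terms for PTH and the bone markers. It would also help to report the range of phase 2 baseline dates, so that readers can judge how much season could matter.

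The date terms cost two degrees of freedom among 84 women and one sentence in the plan. No new data are needed if draw dates are held in the trial records, which is likely but not stated in the article.
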